### 3.3.3 Enrolment and Baseline

#### 3.3.3.1 Baseline data collection

After study inclusion, study personnel will collect the participants' contact details (name, date of birth, address, phone number, e-mail, contact details of the primary care physician and of a surrogate). This is necessary in order to contact the patients for the follow-up phone calls (or a surrogate in case the patient cannot be reached or has cognitive impairment) and to collect outcome data. These identifying data will be securely stored at the local study site and not be entered in the research database. For all eligible and consenting participants, study personnel will prospectively collect baseline data to describe the study population and for use as adjustment variables in statistical analyses. Following baseline data will be collected (**Table 4**): a) demographic data; b) all items of the simplified and original Geneva score, IMPROVE score, and Padua score (**Table 1**); c) comorbidities d) potential contraindications for pharmacological TPX; e) laboratory findings that are relevant concerning VTE or bleeding risk; f) medications at admission with a potential antithrombotic effect; g) treatments during the current hospital stay, including start date and type of TPX, defined as any use of pharmacological (unfractionated or low-molecular-weight heparin, fondaparinux, or direct oral anticoagulants) or mechanical (intermittent pneumatic compression devices or compression stockings) TPX, as well as other treatments potentially affecting risk of HA-VTE or bleeding; h) information on patient's autonomy.

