| Comorbidities                                        |                                 | x                    |                     |                                     |                  |
| Contraindications to pharmacological VTE prophylaxis |                                 | x                    |                     |                                     |                  |
| Laboratory findings                                  |                                 | x                    |                     |                                     |                  |
| Medications at admission                             |                                 | x                    |                     |                                     |                  |
| Treatments since admission                           |                                 | x                    |                     | x                                   | x                |
| Autonomy: modified Barthel Index                     |                                 | x                    |                     | x                                   | x                |
| Pressure sore risk: Braden scale                     |                                 | x                    |                     |                                     |                  |
| Mobility measurements                         |                                 |                      |                     |                                     |                  |
| Distribution of accelerometer & instructions         |                                 | x                    |                     |                                     |                  |
| Accelerometry                                        |                                 |                      |                     |                                     |                  |
| Physician's estimation of physical activity level    |                                 |                      | x                   |                                     |                  |
| Ability to walk                                      |                                 | x                    |                     |                                     |                  |

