| Feasibility Substudy              |                                 |                      |                     |                                     |                  |
| Consent for hypothetical RCT                         |                                 |                      |                     | x                                   |                  |
| Medical Outcomes                              |                                 |                      |                     |                                     |                  |
| Symptomatic HA-VTE                                   |                                 |                      |                     | x                                   | x                |
| All-cause mortality                                  |                                 |                      |                     | x                                   | x                |
| Major bleeding                                       |                                 |                      |                     | x                                   | x                |
| Clinically relevant non-major bleeding               |                                 |                      |                     | x                                   | x                |
| Other study data                              |                                 |                      |                     |                                     |                  |
| Length of hospital stay                              |                                 |                      |                     | x                                   |                  |
| Discharge location                                   |                                 |                      |                     | x                                   |                  |
| Duration of VTE prophylaxis                          |                                 |                      |                     | x                                   |                  |
| Subsequent hospitalizations                          |                                 |                      |                     |                                     | x                |

 Enrolment and baseline visit may take place within 72 hours of admission

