### 3.3.4 Follow-up visit prior to discharge

A follow-up visit will be conducted the day prior to discharge or the day of discharge. Information on the discharge location (home, nursing home, rehabilitation, other hospital), and the date of discharge (in order to assess length of hospital stay) will be obtained from medical records and/or interview of the participant and treating health care personnel (**Table 5**). In addition, potential medical outcome events will be assessed (see section 2.2). Autonomy will be assessed in a face-to-face interview using the modified Barthel Index (see sections 2.2.3 and 3.3.3.1).

Similar to the baseline visit, information on treatments since admission with a focus on pharmacological and mechanical TPX will be assessed in order to determine duration of TPX (**Table 5**).

Study personnel will collect the accelerometer and upload accelerometry data to the database using the relevant software (Geneactiv and R).

In case a patient dies during the hospitalization, study nurses will collect the accelerometer on the day of death. Also, information on the circumstances of death from medical records and interview of the treating physicians will be collected.

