| Autonomy                                                                                                                                                                                                                                                                                                                                                  |
| Modified Barthel Index                                                                                                                                                                                                                                                                                                                                           |
| Treatments since admission                                                                                                                                                                                                                                                                                                                                |
| Pharmacological thromboprophylaxis: type (low molecular weight heparin, unfractionated heparin, fondaparinux, other), start date; mechanical VTE prophylaxis (lower extremity compression stockings/bandages, intermittent pneumatic compression devices); therapeutic anticoagulation, red blood cell transfusions (and date), central venous catheter, surgery |

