#### **4.1.2 Statistical analyses**

Work package 1) Time to event analyses with competing risk methods will be used to assess the prognostic performance of the simplified Geneva score and the other RAMs (**Table 1**) and their association with HA-VTE, with non-VTE death representing the competing risk. We will use a subdistribution hazard model of Fine and Gray to assess the association of the simplified Geneva score and the other RAMs with VTE, calculating subhazard ratios with 95% CIs. These analyses will be adjusted for the use of TPX and study site. Cumulative incidences of HA-VTE in low- and high-risk score patients will be assessed and graphically presented to assess calibration and compare different RAMs. The time-dependent area under the curve (AUC) as well as sensitivity, specificity, and positive and negative predictive values will be calculated for each RAM to assess their accuracy to predict HA-VTE at 90 days using time-dependent receiver operating characteristic (ROC)-curve analysis, taking into account censored data and competing events. Additionally, because some patients will be treated with TPX and thus have a lower risk of VTE, we will perform separate sensitivity analyses in patients with and without TPX. It is possible that a small number of patients will be started on therapeutic dose anticoagulation for reasons other than VTE (e.g. new onset atrial fibrillation) during follow-up; these patients will be censored in the main analysis.

Secondary time-to-event outcomes (major and clinically relevant non-major bleedings) will also be evaluated using competing risk regression. For all-cause mortality, we will use an ordinary Cox regression, for length of stay an accelerated failure time model. Binary outcomes (in-hospital VTE and readmission) will be evaluated using logistic regression. The Barthel-index will be assessed using linear regression. All models will be adjusted for the use of TPX and study site.

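### The main analysis censors at non-VTE therapeutic anticoagulation, but the listed data hold neither its date nor its reason; thromboprophylaxis dates and the time point of thromboprophylaxis status need fixing too

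*Protocol*

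**What the plan says.** **Therapeutic anticoagulation.** Protocol section 4.1.2 foresees that a few patients will start it for reasons other than VTE and rules that "these patients will be censored in the main analysis". At discharge, Table 5 lists "therapeutic anticoagulation, red blood cell transfusions (and date), central venous catheter, surgery": the transfusion entry carries a date, the anticoagulation entry does not, and no indication is asked for. Section 3.3.5 adds new therapeutic anticoagulation since discharge to the 90-day call, again with no date or reason.

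**TPX duration.** Table 3 has its own row, "Duration of VTE prophylaxis", marked at the discharge visit. Section 3.3.4 says that treatment data with a focus on TPX "will be assessed in order to determine duration of TPX" and refers to Table 5. Tables 4 and 5 list type and start date for pharmacological TPX, no stop date, and no date at all for mechanical TPX.

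**TPX status.** Section 3.3.3.1 records "start date and type of TPX, defined as any use of pharmacological" or mechanical prophylaxis, among treatments during the current stay. The same section says that staff "collect baseline data to describe the study population and for use as adjustment variables in statistical analyses". In Table 3, "Treatments since admission" is marked at baseline, discharge and day 90. Section 4.1.2 adjusts all models for TPX use and adds that "we will perform separate sensitivity analyses in patients with and without TPX". Section 3.4 likewise adjusts for receipt of TPX and plans a sensitivity analysis excluding treated patients. None of these places says when a patient's TPX status is determined.

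**The concern.** A censoring rule needs a trigger and a time. Here the trigger is the reason for anticoagulation and the time is its start date. If neither is collected, the primary time-to-event analysis cannot be run as written. A later analysis plan cannot supply dates that nobody asked for, least of all those that depend on a single phone call at 90 days.

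The TPX question is one of classification. Suppose status means any use during the stay. A patient with VTE on day 4 and no TPX so far is then untreated, while an otherwise identical patient who stays event-free and starts TPX on day 5 is treated from the outset. Early events collect in the untreated group, TPX looks protective even if it does nothing, and the adjustment in every risk-score model carries that error. Section 3.4 says that a cohort without TPX would be ideal, so the analysis without TPX is the nearest substitute for it.

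**Working it through.** **1. Fields needed against fields listed**

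| Item | Needed for | Where listed |
|---|---|---|
| Start date of therapeutic anticoagulation | Time of censoring (4.1.2) | Not in Table 5, not in 3.3.5 |
| Reason for therapeutic anticoagulation | Whether to censor (4.1.2) | Not in Table 5, not in 3.3.5 |
| Start date, pharmacological TPX | Status at any chosen time | Tables 4 and 5 |
| Stop date, pharmacological TPX | Duration (Table 3, 3.3.4) | Not in Table 5; duration is its own row in Table 3 |
| Start and stop dates, mechanical TPX | Status and duration | Not in Tables 4 or 5 |

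Section 2.2.3 promises date, type and circumstances only for VTE, bleeding and death. The first two rows concern the main analysis and need no arithmetic.

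**2. Number of events**

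Section 4.1.1 assumes 67% high risk with 2.8% incidence and 33% low risk with 0.6%. Its sample size is not in dispute: a pooled two-proportion calculation at 80% power and two-sided alpha 0.05 gives 1318, against the stated 1308.

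- Expected events: 1350 × (0.67 × 0.028 + 0.33 × 0.006) = 1350 × 0.02074 = 28.0.
- Section 3.4 expects fewer than 60% on TPX. With an assumed 40 to 60% without TPX and the same rates, that stratum has 540 to 810 patients, 11.2 to 16.8 events, and 37 to 55% power for 2.8% against 0.6%.

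**3. Bias if status means ever-use and TPX has no effect**

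Let e be the share on TPX early, q the share of the rest who start late, and F the fraction of 90-day events that fall before a late start. None of these is in the protocol. The assumed ranges are e = 0.4 to 0.5, q from 0.1 upwards, and F = 0.15 to 0.30, with ever-use e + (1 − e)q held to at most 0.60 to respect section 3.4.

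- Multiplier of incidence without TPX: 1 + qF/(1 − q).
- Multiplier of incidence with TPX: [e + (1 − e)q(1 − F)] / [e + (1 − e)q].

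Largest bias under the cap (e = 0.4, q = 1/3, F = 0.30):

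- ever-use = 0.4 + 0.6 × 1/3 = 0.60
- without TPX: 1 + 0.10/0.667 = 1.15
- with TPX: (0.40 + 0.20 × 0.70)/0.60 = 0.90
- with/without risk ratio: 0.90/1.15 = 0.78
- events moved: 0.20 × 28 × 0.30 = 1.7

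Smallest bias (e = 0.5, q = 0.1, F = 0.15):

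- without TPX: 1 + 0.015/0.9 = 1.017
- with TPX: (0.50 + 0.05 × 0.85)/0.55 = 0.986
- with/without risk ratio: 0.986/1.017 = 0.97
- events moved: 0.05 × 28 × 0.15 = 0.2

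**4. A milder set of assumptions**

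Take 60% ever on TPX, 5 to 20% of all patients starting late, and 10 to 30% of events in the start window. With uniform timing, half of the late starters' window events precede the start.

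- Events moved: from 0.05 × 28 × 0.10 × 0.5 = 0.07 to 0.20 × 28 × 0.30 × 0.5 = 0.84.
- At the upper end: without TPX (11.2 + 0.84)/(540 + 0.84) = 2.23%; with TPX (16.8 − 0.84)/(810 − 0.84) = 1.97%; without/with ratio 1.13.
- At the lower end the ratio is 1.01.

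**The case against.** Several points on the other side stand.

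- **Ever-use is an inference.** A reader might infer that the protocol fixes TPX as one yes/no value over the whole stay. In section 3.3.3.1 the phrase about any use mainly says which modalities count, and it stands in a list of baseline adjustment variables. A baseline reading would largely remove selection on later events, and landmark or time-varying coding is what an analysis plan commonly settles. Baseline is not a fixed clock point, though: the footnote to Table 3 allows it up to 72 hours after admission.
- **Duration is scheduled.** A reader might infer that TPX duration is unobtainable for everyone. It is its own item in Table 3, and for pharmacological TPX a start date plus a duration gives the stop date. What remains is that Table 5 omits a field that Table 3 and section 3.3.4 require.
- **The window for bias is narrow.** Section 3.3.3.2 expects most TPX decisions by the second hospital day, section 2.2.1 does not count VTE in the first 48 hours, and the with/without split is a sensitivity analysis.
- **Larger figures are tempting.** With e = q = 0.4 and F = 0.30 the risk ratio is 0.74 and the overstatement 20%. That implies 0.4 + 0.6 × 0.4 = 64% ever treated, against fewer than 60% in section 3.4. One might also infer that the score's high/low contrast is inflated because high-risk patients start late more often. Section 3.4 expects treated and untreated patients to be well distributed over the risk groups, and section 3.3.3.1 says physicians are not told the scores.
- **The censoring gap may affect few patients.** Section 4.1.2 expects a small number, need for therapeutic anticoagulation is an exclusion criterion, and the operations manual or electronic form may hold more fields. In a patient with no adjudicated VTE the reason might be guessed, but the date cannot be.

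The last point limits the reach of the censoring gap without closing it. The protocol assigns dates item by item and gives none here.

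**Conclusion.** The point holds, with the data items leading. As listed, the fields cannot trigger or time the censoring that the main analysis prescribes. The number affected is not given and is expected to be small, so no size is put on it. Nor do the documents show that follow-up will actually be misassigned, only that the listed items do not prevent it.

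Table 3 and section 3.3.4 on one side and Table 5 on the other must be reconciled on TPX duration, and mechanical TPX is undated throughout.

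The time point of TPX status is open. Only under the ever-use reading does group membership depend on later events, and the effect is probably small: a spurious with/without risk ratio of about 0.78 to 0.97 and incidence without TPX overstated by about 2 to 15%, or a without/with ratio of 1.01 to 1.13 under milder assumptions. All of these rest on assumed shares of late starters and assumed event timing. They amount to between less than 0.1 and 1.7 events out of 28, which still counts in a stratum of 11 to 17.

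**What to change.** 1. Add start date and indication of therapeutic anticoagulation to Table 5 and to the 90-day call, and state that censoring occurs at that start date.
2. Add the TPX stop date to Table 5, and start and stop dates of mechanical TPX to Tables 4 and 5, so that they agree with Table 3 and section 3.3.4.
3. In sections 3.4 and 4.1.2, define TPX for adjustment and for the with/without analyses by status at 48 hours after admission, when outcome counting begins. Handle later starts as a time-dependent covariate, or by censoring at TPX start in the analysis without TPX. For mechanical TPX this depends on item 2, since its start dates are not now listed.

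The cost is a few more fields in the electronic case report form and some wording on the analysis. The inpatient fields come from the chart. The post-discharge anticoagulation date and reason have to be asked for in the phone call, so they take a little more effort and may be less exact.

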**Table 4. Baseline data collection**

|                                                                                                                                                                                                                                                                                                                                                                                                                                                                                                                                                                                                                                                                                                   |
|---------------------------------------------------------------------------------------------------------------------------------------------------------------------------------------------------------------------------------------------------------------------------------------------------------------------------------------------------------------------------------------------------------------------------------------------------------------------------------------------------------------------------------------------------------------------------------------------------------------------------------------------------------------------------------------------------|
| Demographic characteristics                                                                                                                                                                                                                                                                                                                                                                                                                                                                                                                                                                                                                                                                |
| Sex, year of birth, date of admission, date of inclusion, body weight, height, setting prior to admission                                                                                                                                                                                                                                                                                                                                                                                                                                                                                                                                                                                         |
| Items of the risk assessment models                                                                                                                                                                                                                                                                                                                                                                                                                                                                                                                                                                                                                                                        |
| Previous VTE, hypercoagulable state/thrombophilia, active cancer, history of cancer within last 5 years, myeloproliferative syndrome, cardiac failure, respiratory failure, acute infection, rheumatologic disorder, immobilization (bed rest with bathroom privileges) $\geq 72$ hours, estimated immobilization $> 7d$ , stroke (and date of event), myocardial infarction (and date of event), recent ( $\leq 1$ month) trauma or surgery (and date of event), ongoing hormonal treatment, lower extremity paralysis/paresis, stay in the intensive care unit / intermediate care unit, nephrotic syndrome, recent travel ( $> 6$ hours), chronic venous insufficiency, pregnancy, dehydration |
| Other potential VTE risk factors                                                                                                                                                                                                                                                                                                                                                                                                                                                                                                                                                                                                                                              |
| Heart rate, body temperature, leg edema, active tobacco use                                                                                                                                                                                                                                                                                                                                                                                                                                                                                                                                                                                                                                       |
| Comorbidities                                                                                                                                                                                                                                                                                                                                                                                                                                                                                                                                                                                                                                                                 |
| History of myocardial infarction, congestive heart failure, peripheral vascular disease, cerebrovascular disease, dementia, chronic obstructive pulmonary disease, connective tissue disease, peptic ulcer disease, liver disease, diabetes mellitus, hemiplegia, chronic kidney disease, localized solid tumor, metastatic solid tumor, leukemia, lymphoma, AIDS, gastroduodenal ulcer, history of bleeding, inflammatory bowel disease, blood dyscrasias, anemia; number of comorbidities; risk of bedsores (using the Braden scale)                                                                                                                                                            |
| Contraindications to pharmacological VTE prophylaxis                                                                                                                                                                                                                                                                                                                                                                                                                                                                                                                                                                                                                                       |
| Known hypersensitivity to heparin, history of heparin induced thrombocytopenia, liver failure, active non-major or major bleeding (and date of event), hemorrhagic transformation of acute ischemic stroke (and date of event)                                                                                                                                                                                                                                                                                                                                                                                                                                                                    |
| Laboratory findings                                                                                                                                                                                                                                                                                                                                                                                                                                                                                                                                                                                                                                                                        |
| Platelet count, international normalized ratio (INR), serum creatinine, hemoglobin, leukocytes, CRP, D-Dimer, fibrinogen                                                                                                                                                                                                                                                                                                                                                                                                                                                                                                                                                                          |
| Medications at admission                                                                                                                                                                                                                                                                                                                                                                                                                                                                                                                                                                                                                                                                   |
| aspirin, other antiplatelet therapy (clopidogrel, prasugrel, ticagrelor), nonsteroidal antiinflammatory drugs (NSAIDs)                                                                                                                                                                                                                                                                                                                                                                                                                                                                                                                                                                            |
| Treatments during hospital stay                                                                                                                                                                                                                                                                                                                                                                                                                                                                                                                                                                                                                                                            |
| Pharmacological thromboprophylaxis: type (low molecular weight heparin, unfractionated heparin, fondaparinux, other), start date; mechanical VTE prophylaxis (lower extremity compression stockings/bandages, intermittent pneumatic compression devices); red blood cell transfusions (and date), central venous catheter                                                                                                                                                                                                                                                                                                                                                                        |

